## Abstract

**Background:**

Patients with rheumatoid arthritis (RA) who have undergone total knee arthroplasty are at increased risk of requiring a blood transfusion. This study is designed to compare the effects of preemptive antifibrinolysis of single-dose and repeat-dose tranexamic acid (TXA) in in RA patients undergoing total knee arthroplasty (TKA).

**Methods/design:**

The study will be a double-blind randomized controlled trial with two parallel groups of RA patients. Group A will be given 100 ml normal saline twice daily starting from 3 days before the operation, Group B will be given TXA 1.5 g twice daily starting from 3 days before the operation. All patients will be given TXA 1.5 g 30 min before the operation. The primary outcomes will be evaluated with total blood loss and hidden blood loss. Other outcome measurements such as, fibrinolysis parameters, inflammatory factors, visual analogue scale for post-operative pain, analgesia usage, coagulation parameters, transfusion, the length of stay (LOS), total hospitalization costs, the incidence of thromboembolic events and other complications will be recorded and compared. Recruitment is scheduled to begin on 1 August 2020, and the study will continue until 31 May 2021.

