### Primary outcomes

#### Perioperative blood loss

The patient’s blood volume (PBV) and perioperative blood loss are calculated according to Nadle et al. [28] and Gross formula [29]:

The patient’s blood volume (PBV) [28] = k1 × height (m) + k2 × weight (kg) + k3 (male: k1 = 0.3669, k2 = 0.03219, k3 = 0.6041; female: k1 = 0.3561, k2 = 0.03308, k3 = 0.1833 for women).

The total blood loss (TBL) [29] = PBV × (Hct_pre_ − Hct_post_)/ Hct_ave_ (Hct_pre_ = preoperative hematocrit level. Hct_post_ = the lowest postoperative hematocrit level during hospitalization. Hct_ave_ = the average of the Hct_pre_ and Hct_post_).

The intraoperative blood loss (IBL) [30] = (the weight of the gauze pads and compresses with blood – the dry weight of the gauze pads and compresses) + (the volume collected by the aspirators – the volume used to wash the surgical area).

The hidden blood loss (HBL) [31] = TBL – measured blood loss (measured blood loss mainly included IBL and the volume of drainage).

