### Sample size calculation

Sample size was estimated based on a large database generated from a prospective multicenter study sponsored by the Chinese Health Ministry (project number 201302007) using PASS 2011 (NCSS, LLC. Kaysville, Utah, USA) software. According to the database, the TBL was 730.96 ± 262.85 mL, with a single dose of TXA before TKA in RA patients. To detect a difference of 200 mL of primary end point, with a power of 0.90 and the significance level of 0.05, 31 patients per arm will be needed. Considering a dropout rate of 20%, we decided to involve 39 patients in each arm.

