### Statistical analysis

Statistical analyses will be performed using SPSS version 24 (SPSS Inc. USA) software. We will use the independent samples t-test (Student’s t-test) to evaluate quantitative data with normal distribution, and use Mann–Whitney U-test for data not having normal distribution. Pearson Chi-square test or Fisher exact test will be used to analyze qualitative comparative data. *P* values will be judged significant if they are less than 0.05.

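### Two unranked primary outcomes (TBL and HBL) are judged at 0.05 each, while the sample size supports TBL alone

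*Protocol article*

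**What the plan says.** The abstract (Methods/design) states: "The primary outcomes will be evaluated with total blood loss and hidden blood loss". The Primary outcomes section gives the formulas and does not rank them. TBL uses "the lowest postoperative hematocrit level during hospitalization", which yields one value per patient. HBL is derived from it as "TBL – measured blood loss (measured blood loss mainly included IBL and the volume of drainage".

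The Sample size calculation refers to a single end point. Its planning figures are for TBL: "the TBL was 730.96 ± 262.85 mL, with a single dose of TXA before TKA in RA patients". The target is worded: "To detect a difference of 200 mL of primary end point, with a power of 0.90 and the significance level of 0.05". No SD, target difference or power is given for HBL.

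The Statistical analysis section sets the test ("We will use the independent samples t-test (Student’s t-test) to evaluate quantitative data with normal distribution", with Mann–Whitney as the alternative) and one criterion for all comparisons: P "values will be judged significant if they are less than 0.05". It states no hierarchy, correction or joint-success rule.

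Table 1 marks TBL and HBL under each of the first three postoperative days.

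**The concern.** The abstract has two primary outcomes; the sample size has one. The difference matters most when the results disagree. If HBL reaches P < 0.05 and TBL does not, or the reverse, the document cannot say whether the trial succeeded. The trial is meant to inform recommendations on TXA in RA patients, so that question should have one answer fixed in advance.

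Two consequences follow. If either outcome may carry the claim, the false-positive risk on the primary question exceeds the nominal 5%. And one of the two outcomes called primary has no planning basis, so a non-significant HBL result could not be interpreted against any stated power.

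**Working it through.** **Inputs.** From the Sample size calculation: SD 262.85 mL, difference 200 mL, power 0.90, alpha 0.05 (sidedness not stated), 31 per arm, 39 per arm after 20% dropout. From the abstract: two primary outcomes. From Statistical analysis: 0.05 for each. The TBL-HBL correlation is not given, so a range is assumed.

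**1. The plan's own figure.** By the normal approximation, n per arm = 2(z_alpha + z_beta)² (SD/difference)², with (262.85/200)² = 1.727.
- One-sided 0.05: 2 × (1.645 + 1.282)² × 1.727 ≈ 29.6, so 30. The exact noncentral t gives 31, and 31/0.8 = 38.75, so 39. This matches the plan.
- Two-sided 0.05: 2 × (1.960 + 1.282)² × 1.727 ≈ 36.3, so 37. The exact t gives 38, or 48 after dropout. This does not match.

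The stated size therefore reproduces for TBL alone, and only with a one-sided test. Sidedness is a separate point; it matters here only for choosing the right power baseline in step 3.

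**2. Family-wise error if success on either outcome counts.** Each test is taken as two-sided at 0.05, so the error is 1 − P(|Z1| < 1.96 and |Z2| < 1.96) under the null for both. Both tests use the same patients, so the correlation of the two statistics is approximately the within-arm correlation of the two outcomes.

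| Assumed correlation | Error |
|---|---|
| 0 (independent: 1 − 0.95²) | 9.75% |
| 0.5 | 9.1% |
| 0.7 | 8.4% |
| 0.8 | 7.8% |
| 0.9 | 7.0% |
| 0.95 | 6.5% |

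HBL is computed from TBL, so a positive correlation is expected and 9.75% serves as an upper reference. The error stays above 5% for any correlation below 1. If both outcomes had to be significant, it could not exceed 5%, because a false claim would need the truly null outcome to cross its own 0.05 threshold.

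**3. Two ways to hold 5%.**
- *Fixed order, TBL then HBL.* If TBL is truly null, a false claim requires TBL to cross 0.05, which has probability 5%. If TBL is not null, only HBL can be falsely declared, again at most 5%. Alpha is not split and TBL power is untouched.
- *Bonferroni, two-sided 0.025 each.* TBL power by the exact t, for the planned difference and SD:

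| Evaluable per arm | Two-sided 0.05 | Two-sided 0.025 |
|---|---|---|
| 31 | 83.8% | 75.5% |
| 39 | 91.3% | 85.6% |

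Reaching 90% for TBL at two-sided 0.025 would need 45 evaluable per arm (45/0.8 = 56.25, so 57 with dropout).

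**The case against.** The strongest reply is that the inflation is modest and conditional. It needs the either-outcome reading, which the document does not state, and a correlation it does not supply. Testing order is often left to a statistical analysis plan, which is not shown, and the singular end point in the sample size already points to TBL. Much of this stands: the figures are a range under assumptions, and silence about a correction would not on its own be a finding in a condensed article. What remains is a conflict within the document, which names two primary outcomes in one place, sizes for one in another, and applies a single threshold to all.

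Several stronger readings are tempting but unsupported.

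- *Six primary tests.* From Table 1 a reader might infer that both outcomes are tested on each of three days, which under assumed correlations would give an error of about 13% to 21%. Table 1 schedules assessments, not tests, and has no hematocrit row, so the marks may simply show the sampling days from which the lowest value is taken. The TBL definition gives one value per patient. That range is not this trial's error rate.
- *Intraoperative blood loss as a third primary.* It appears under the primary heading as an input to HBL, just as blood volume is an input to TBL. The abstract does not name it as primary.
- *Measurement noise creating false positives.* Gauze, suction and drain error unrelated to arm lowers power; it does not raise the type I error of a 0.05 test. The plan blinds patients, surgical team and investigators, and no differential error is shown.
- *Bonferroni cutting power from 90% to 75.5%.* At 31 per arm the two-sided starting point is 83.8%. The rest of the gap comes from sidedness, not from the split.

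**Conclusion.** The point holds in a limited form. The document names TBL and HBL as unranked primary outcomes, judges each at 0.05, and sizes the trial on TBL only. If success on either counts, the family-wise error is about 6.5% to 9.1%. This rests on two-sided tests and an assumed correlation of 0.95 to 0.5. Under a both-must-succeed rule there is no inflation, but the power for that joint claim could not be stated, because HBL has no planning figures. Leaving the success rule open is the defect, and it bears on the main conclusion, so it should be settled before unblinding. The conclusion does not depend on the daily marks in Table 1.

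**What to change.** - Name TBL as the single primary outcome, one value per patient under the existing definition (lowest in-hospital postoperative hematocrit). This matches the sample size. The in-hospital window need not change.
- Make HBL the key secondary outcome, tested at 0.05 only if TBL is significant.
- State that any day 1 to day 3 values of TBL or HBL in Table 1 are descriptive.
- Align the abstract, Table 1, the Primary outcomes section and the Sample size calculation with this.

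A fixed order is preferable to a Bonferroni split because it leaves TBL power intact. The cost is protocol wording and a matching registry update before unblinding, with no added patients. The downside is that HBL loses its stand-alone primary status: if TBL is not significant, HBL cannot support a confirmatory claim.

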**Discussion:**

In current literature there is a lack of evidence with regard to the efficacy of TXA in RA patients. The findings of this study, whether positive or negative, will contribute to the formulation of further recommendations on the use of TXA in RA patients undergoing TKA.

**Trial registration:**

Chinese Clinical Trial Registry, ChiCTR2000029720. Registered 14 February 2020.

## Background

As the one of the most common inflammatory arthritis affecting about 1% of world population [1, 2], rheumatoid arthritis (RA) is associated with an increasing socioeconomic impact and often affects the diarthrodial joints, including knee joint [3, 4]. Total knee arthroplasty (TKA) is considered one of the most effective orthopedic health care interventions for patients with rheumatoid arthritis (RA) [5–8], and RA patients achieve better satisfaction after TKA compared to patients with osteoarthritis (OA) [8]. However, fibrinolysis stimulated by surgical trauma could lead to significant blood loss [9, 10], and RA patients undergoing this procedure tend to have a higher risk of requiring transfusion than OA patients, owing to preoperative anemia, lower average weight, great bone mass loss, complete synovectomy and extensive soft tissue separation [11, 12]. Blood transfusion is often associated with infectious or noninfectious complications [13], and can prolonged hospital stays, delay recovery and increase medical expenses [14]. Therefore, decreasing blood loss, which can subsequently reduce the requirement for transfusion, is extremely important for patient to improve the quality of life.

As an antifibrinolytic agent, the hemostatic effect of tranexamic acid (TXA) has been proven in TKA [9, 10, 15]. However, in view of the fact that almost 97% of TKAs are performed for OA [16], current published studies in terms of the efficacy of TXA were mainly based on the experience in OA patients [9, 17–20], and there still exists a paucity of evidence with regard to the efficacy of TXA in RA patients. Unlike OA, RA has its own features in the aspects of pathogenesis, prognosis, and medical management [5]. It has been reported that RA patients had higher preoperative D-dimer value than OA patients [21]. Therefore, TXA is theoretically more suitable for RA patients compared to OA patients, and a specially designed TXA scheme for RA patients with TKA is urgently needed.

The most common preoperative protocol of TXA in TKA is to administer one single dose prior to skin incision [9, 22–24], which might seem to be insufficient to inhibit fibrinolysis in RA patients. Therefore, we plan to conduct a randomized clinical trial to compare the effects of preemptive antifibrinolysis of single-dose and repeat-dose TXA in RA patients undergoing TKA.

## Methods

### Study design

The study will be a randomized, prospective, double-blind (patient and evaluator) clinical trial. This study has been approved, and conforms to the Declaration of Helsinki. The trial has been registered at the Chinese Clinical Trial Registry (ChiCTR2000029798). Informed consent will be obtained. The schedule of trial enrolment and assessments is shown in Table 1. The trial flow chart is shown in Fig. 1.

**Table 1 Tab1:** The schedule of trial enrolment and assessments

	Study period								
	Pre-D3	Pre-D1	OP	D1	D2	D3	DOD	D14	D90
**Enrolment**									
Eligibility screen	●								
Informed consent	●								
Randomization	●								
**Outcome assessment**									
TBL				●	●	●			
IBL			●						
HBL				●	●	●			
Hemoglobin level	●	●		●	●	●		●	
Fibrinolysis parameters	●	●		●	●	●		●	
Inflammatory markers	●	●		●	●	●		●	
Coagulation parameters	●	●		●	●	●		●	
Pain level	●	●		●	●	●		●	
Analgesia usage				●	●	●			
Knee range of motion	●	●		●	●	●		●	●
LOS						●			
Hospitalization costs						●			
DVT						●		●	●
PE						●		●	●
Adverse events				●	●	●	●	●	●

Pre-D3, 3 days before surgery; Pre-D1, 1 day before surgery; OP, operative; TBL, total blood loss; IBL, intraoperative blood loss; HBL, hidden blood loss; LOS, length of stay; DVP, deep vein thrombosis; PE, pulmonary embolism; D1, the 1st day after surgery; D2, the 2nd day after surgery; D3, the 3rd day after surgery; DOD, the day of discharge; D14, the 14th day after surgery; D90, the 90th day after surgery

**Fig. 1 Fig1:**
[figure not shown]
The study flow diagram, including participants recruitment, eligibility, screening, randomization, allocation concealment and outcome assessments. TXA, tranexamic acid

### Inclusion criteria

The patient is diagnosed with RA in Stage III or IV according to the Kellgren-Lawrence classification [26];The patient will sign informed consent;The patient will undergo the unilateral primary TKA.

### Exclusion criteria

A history of a thromboembolic event;Received anticoagulant therapy (warfarin or heparin) within the previous week;Cardiovascular problems or cerebrovascular conditions (history of myocardial infarction, angina, atrial fibrillation, or previous stroke);An acquired or congenital coagulopathy;Allergy to TXA.

### Termination criteria

The patient will be terminated under the following conditions: (1) Shock; (2) Seizure; (3) Digestive disorders, such as nausea, vomiting and diarrhea after administration; (4) Embolic events, such as pulmonary embolism.

### Perioperative anti-rheumatic treatment

Nonbiologic disease-modifying antirheumatic drugs (DMARDs) such as methotrexate, hydroxychloroquine, leflunomide, and/or sulfasalazine, will be used throughout the perioperative period. Biologic agents will be withheld prior to TKA and surgery will be planned at the end of the dosing cycle for that specific medication. The biologic therapy will be restarted when the wound shows evidence of healing without surgical site infections (typically two weeks after TKA) [27].

### Study interventions

Group A: 100 mL normal saline (NS) will be administrated intravenously twice daily starting from 3 days before the operation (performed by a nurse). 1.5 g of TXA will be given 30 min before the operation (performed by an anesthetist).Group B: 1.5 g of TXA will be given twice daily starting from 3 days before the operation (performed by a nurse). 1.5 g of TXA will be given 30 min before the operation (performed by an anesthetist).

TXA is produced by Chongqing Lummy Pharmaceutical Co., Ltd., and used according to the second edition of 2015 Chinese Pharmacopoeia and Drug Supplement Application Approval YBH19712005; the approval number is National Drug Standard H20056600.

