#### Adverse events

Each patient will be screened with clinical symptoms (acute onset, swelling, sever pain) and physical examination (significant tenderness at the femoral triangle or/and leg) to ensure no deep vein thrombosis (DVT) is present. Doppler ultrasound in diagnosis of venous thrombosis of lower extremities will be performed at the time of hospital discharge, and repeated at 2 weeks and 3 months after TKA.

Pulmonary embolism (PE) will be investigated by clinical signs and symptoms (cough, hemoptysis, chest tightness, tachypnea, shock, dizziness, cyanosis, etc.). Patient with clinically suspected PE will undergo a contrast-enhanced chest CT scan immediately.

The wound complications (ecchymosis, bleeding, local hematoma, superficial and deep infection) will be carefully recorded during hospitalization and follow-up period.

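### Table 1 schedules adverse-event assessment only from the first postoperative day, although the arms differ only in the infusions given before surgery

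*Protocol article*

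**What the plan says.** **Treatment.** The protocol article, Study interventions, gives Group A as "100 mL normal saline (NS) will be administrated intravenously twice daily starting from 3 days before the operation" and Group B as "1.5 g of TXA will be given twice daily starting from 3 days before the operation". The abstract adds what is common to both arms: "All patients will be given TXA 1.5 g 30 min before the operation".

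**Schedule.** Table 1 has nine columns. Its footnote defines the first three as "Pre-D3, 3 days before surgery; Pre-D1, 1 day before surgery; OP, operative" and the fourth as "D1, the 1st day after surgery". The row "Adverse events" is marked at D1, D2, D3, DOD, D14 and D90 and is empty at Pre-D3, Pre-D1 and OP.

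**Harms the protocol names.** Termination criteria lists shock, seizure, embolic events and "Digestive disorders, such as nausea, vomiting and diarrhea after administration". The Adverse events section covers DVT, PE and wound complications. Of the Doppler scan it says that it "will be performed at the time of hospital discharge, and repeated at 2 weeks and 3 months after TKA".

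**Aim.** The Discussion states that evaluating the safety of the TXA regimens in RA patients is one purpose of the trial.

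**The concern.** A safety comparison should observe patients while they receive the treatment that separates the arms. Here that treatment is given entirely before the operation, and the first scheduled adverse-event assessment falls on the day after it.

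The protocol itself foresees digestive symptoms following administration, since it makes them a ground for termination. Yet on the days when only Group B receives active drug, Table 1 schedules no assessment that would record such symptoms as outcomes. A patient who vomits after an infusion two days before surgery and is well by the operation has no scheduled visit at which this is written down.

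Nausea first recorded on D1 follows general anaesthesia and PCIA in both arms and says little about the earlier infusions. At stake is whether the trial can report on the short-lived tolerability of repeat dosing.

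**Working it through.** The plan gives no figure on this point, so the check sets the treatment timetable against the assessment timetable.

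**1. Where the arms differ.**

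| Period | Group A | Group B | Arms differ? |
|---|---|---|---|
| From 3 days before surgery | saline twice daily | TXA twice daily | yes |
| 30 min before surgery | TXA | TXA, same dose | no |
| After surgery | common care | common care | no |

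**2. Where adverse events are assessed (Table 1).**

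| | Pre-D3 | Pre-D1 | OP | D1 | D2 | D3 | DOD | D14 | D90 |
|---|---|---|---|---|---|---|---|---|---|
| Adverse events | – | – | – | ● | ● | ● | ● | ● | ● |

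That is 0 of 3 columns up to and including surgery and 6 of 6 after it.

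**3. Is the alignment safe?** Yes. The single mark for intraoperative blood loss falls under OP, where it must be, and total blood loss starts under D1. Six other rows (hemoglobin, fibrinolysis, inflammation, coagulation, pain, knee range of motion) are marked at both Pre-D3 and Pre-D1. The preoperative columns were in use and the adverse-event row does not use them.

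**4. Exposure before the first assessment.** The total number of infusions is not stated. Assuming two a day for three full days, it is 2 × 3 = 6 per patient, or 39 × 6 = 234 active infusions in Group B. One fewer or one more per patient gives 39 × 5 = 195 or 39 × 7 = 273. This counts doses, not missed events.

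**5. Direction of the effect.** Let p_A and p_B be the true risks of a transient event that starts and resolves before D1. Let c be the probability that such an event is recorded, equal in both arms under blinding. The expected recorded difference is

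c × (p_B − p_A).

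At c = 1 the whole difference is seen, at c = 0.5 half of it, at c = 0 none. The document does not allow c to be estimated, so the range is 0 to 1. With any c below 1 the difference shrinks towards zero.

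Postoperative events common to both arms, with risk b, cancel from the risk difference, so they add noise but not bias to it. If the two kinds of event are pooled and treated as additive, the ratio (b + c·p_B)/(b + c·p_A) moves towards 1 as c falls.

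**6. Which outcomes are exposed to this.**
- Transient nausea, vomiting, diarrhoea or seizure before D1: yes.
- Thrombosis that begins before surgery: largely not, because it may still be found on a later Doppler. The article states no preoperative scan, so its onset could not be dated.
- Wound complications: no, since they cannot precede the incision.
- Total and hidden blood loss: no.

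**The case against.** The strongest reply is that an empty cell in an assessment table does not mean that an event goes unrecorded. Table 1 is not a full list of what is recorded: it has no row for transfusion or wound complications, yet the text says that both are recorded throughout the hospital stay and follow-up. Staff could not apply the termination criteria without noticing shock, seizure, digestive upset or embolism on the infusion days. Symptom screening for DVT and PE is not limited in the text to the postoperative period. Coagulation tests, which the Discussion names as a means of assessing safety, are drawn at Pre-D3 and Pre-D1.

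Much of this stands, and it rules out three stronger readings.

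- *Preoperative harms are not collected at all, or capture is close to zero.* A reader might infer this from the blank cells, but they show only that no assessment is scheduled. Severe events would probably be noticed, and nothing in the document supports a capture rate.
- *The whole safety comparison is biased towards no difference.* This holds only for events that are over before D1.
- *The protocol describes all its termination events as following administration.* In the text that qualifier belongs to the digestive disorders only.

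What the reply does not supply is a scheduled record of symptoms on the infusion days. A termination rule identifies patients to withdraw; it does not say when, or for whom, the event is recorded as an outcome. Laboratory markers do not record vomiting or a seizure. The full protocol may hold CRF detail that the article condenses, but Table 1 states a schedule, and that schedule fits the design badly.

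**Conclusion.** The point holds in a limited form. Scheduled adverse-event assessment begins at D1, after the randomised difference in treatment has ended, and none is scheduled in the three columns up to and including surgery. For transient, infusion-related events that resolve before D1, the comparison is incomplete and tends towards no difference, by a factor that the document does not let us compute.

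This rests on reading Table 1 as the operative schedule and on equal recording in both blinded arms. The primary analysis is untouched, and with 39 patients per arm, sized on total blood loss, clinical adverse events will be largely descriptive in any case. It should still be corrected, because safety is a declared aim and unrecorded symptoms on dosing days may not be recoverable later.

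A minor mismatch sits beside it: Table 1 marks DVT at D3 and leaves DOD empty, while the text ties the first Doppler to discharge. Length of stay and costs are also marked at D3, so that column may be standing in for discharge.

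**What to change.** - Mark the adverse-event row of Table 1 at Pre-D3, Pre-D1 and OP, and state that recording starts at the first study infusion and is done at each infusion attendance.
- State that events leading to termination before surgery are recorded and counted by randomised arm.
- Report events from first infusion to surgery separately from those after surgery.
- Reconcile the D3 mark for DVT in Table 1 with the discharge Doppler in the Adverse events section.

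The cost is a table change and a small amount of added CRF recording. A nurse already gives the infusions twice daily, so no extra visit or procedure is needed, and no dose or clinical rule changes.
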